## Abstract

**Background:**

Women with insulin-treated gestational diabetes mellitus (GDM) require close monitoring and support to manage their diabetes. Recent changes to the diagnostic criteria have implications for service provision stemming from increased prevalence, suggesting an increased burden on health services in the future. Telemedicine may augment usual care and mitigate service burdens without compromising clinical outcomes but evidence in GDM is limited.

**Objective:**

The Telemedicine for Gestational Diabetes Mellitus (TeleGDM) trial aims to explore the use of telemedicine in supporting care and management of women with GDM treated with insulin.

**Methods:**

The TeleGDM is a mixed-methods study comprising an exploratory randomized controlled trial (RCT) and a qualitative evaluation using semistructured interviews. It involves women with insulin-treated GDM who are up to 35 weeks gestation. Participating patients (n=100) are recruited face-to-face in outpatient GDM clinics at an outer metropolitan tertiary hospital with a culturally diverse catchment and a regional tertiary hospital. The second group of participants (n=8) comprises Credentialed Diabetes Educator Registered Nurses involved in routine care of the women with GDM at the participating clinics. The RCT involves use of a Web-based patient-controlled personal health record for GDM data sharing between patients and clinicians compared to usual care. Outcomes include service utilization, maternal and fetal outcomes (eg, glycemic control, 2nd and 3rd trimester fetal size, type of delivery, baby birth weight), diabetes self-efficacy, satisfaction, and costs. Semistructured interviews will be used to examine user experiences and acceptability of telemedicine.

**Results:**

The trial recruitment is currently underway. Results are expected by the end of 2016 and will be reported in a follow-up paper.

**Conclusions:**

Innovative use of technology in supporting usual care delivery in women with GDM may facilitate timely access to GDM monitoring data and mitigate care burdens without compromising maternal and fetal outcomes. The intervention may potentially reduce health service utilization.

**Trial Registration:**

Australian and New Zealand Clinical Trials Registry (ANZCTR): ACTRN12614000934640; https://www.anzctr.org.au/Trial/Registration/TrialReview.aspx?id=366740 (Archived by WebCite® at http://www.webcitation.org/6jRiqzjSv).

## Introduction

Recent changes to tighten the diagnostic criteria for gestational diabetes mellitus (GDM) [1] mean many more women will be diagnosed with this condition, placing increased demand on clinical services to provide diabetes care. Women with insulin-treated GDM, in particular, often require more intensive follow-up and support for titration of insulin and overall management of GDM [2,3].

The prevalence of GDM is estimated to be 6% to 15% of pregnancies [1,4] dependent on whether the diagnostic criteria set by the International Association of Diabetes and Pregnancy Study Groups (IADPSG) or the Australasian Diabetes in Pregnancy Society (ADIPS) is used. The IADPSG’s revisions in recent years give higher prevalence estimates [1].

Good control of blood glucose level (BGL) in GDM is important to minimize the risk of pregnancy and birth complications associated with the condition. Such complications can include large for gestational age (LGA) babies, macrosomia, increased likelihood of cesarean delivery, preeclampsia, and fetal shoulder dystocia [3-5]. First-line therapy to control hyperglycemia involves dietary modification and physical activity [1,3,6] or oral hypoglycemic agents (OHA) [3]. An insulin regimen is initiated if the OHA therapies are inadequate in optimizing BGL or there is evidence of increased risk of macrosomia [6]. Approximately 50% of women with GDM go on insulin regimen, which requires close monitoring and intensive follow-up for regular insulin titrations to control persisting hyperglycemia [2].

The increasing prevalence of GDM [7-10] and the intensive clinical care needed have implications for the capacity of health care services to provide timely care and the clinical outcomes of such care. There is a need to explore innovative ways to deliver care and support for women with GDM to ease the service burden while not compromising quality of care. This may also potentially deliver cost efficiencies and savings.

In our systematic review [11], telemedicine has emerged as a potentially effective intervention to address service utilization while producing maternal and fetal outcomes similar to or better than usual care.

Telemedicine is defined as “the use of telecommunications technology to provide medical information and service” [12]. Telemedicine (also known as telehealth) has been implemented as a monitoring intervention in diabetes, heart failure, and chronic obstructive pulmonary disease [9,10,13] with promising results. For instance, a small study that trialled the use of cellular phones to transmit self-monitoring blood glucose data in type 2 diabetes found the approach was feasible, easy to use, and resulted in patients having fewer hospital visits [8]. Recent studies exploring a smartphone application or text messaging in type 1 and/or 2 diabetes reported improvements in glycemic control in favor of the telehealth approaches [14,15], while self-efficacy and quality of life were unchanged [14]. A study of telemedicine in heart failure patients reported better quality of life and heart failure self-care while hospital utilization remained unchanged [13]. While there may be some cautious optimism about the benefits of telehealth-based interventions, usage by patients appears modest, approximately 34% to 39% [16]. It remains to be seen how all this translates to GDM, especially in a real-world clinical setting.

Specifically in GDM, telemedicine interventions compared to control/usual care may reduce service utilization such as face-to-face clinic visits (4.25 [standard deviation or SD 0.93] vs 6.22 [SD 1.48], respectively; *P*=.002) and unscheduled visits (0.50 [SD 0.73] vs 2.89 [SD 1.05], respectively; *P*<.001) [12], while achieving similar outcomes (with trends in favor of telemedicine) for glycemic control, birth weight, incidence of macrosomia [11,12,17,18] and diabetes self-efficacy [12,17-19]. The main limitations of studies of telemedicine in GDM that we identified in our systematic review of the literature [11] are that there are very few randomized controlled trials (RCT) and sample sizes tend to be small. None of the trials included in our review evaluated costs, perhaps due to the lack of an agreed standardized evaluation framework for telehealth interventions. We also identified other methodological limitations such as shorter interventions and the heterogeneous nature of the outcomes and telehealth interventions used [10,20-22]. Interventions were perhaps too short to have significant measurable impacts; outcome measures varied across studies, posing challenges to conducting effects through pooled data analysis, and the interventions varied considerably, ranging from telephone support and videoconferencing to text messaging [10,20-22], making comparison of studies and generalizability difficult.

Our innovative study, the Telemedicine for Gestational Diabetes Mellitus (TeleGDM) trial, uses a Web-based approach to augment the management of women with insulin-treated GDM. Our aim is to explore the effects of telemedicine on health system performances including patient utilization of outpatient clinical care, maternal and fetal clinical health outcomes, and patient and clinician satisfaction and acceptance with respect to the intervention technology. In addition, a cost comparison between the two arms of the trial will be performed to determine if there are any provider cost savings that might be associated with changes in outpatient clinic attendance.

We hypothesize that with timely access to patient GDM self-monitoring data, health service utilization would be decreased without compromising maternal and fetal outcomes with an associated provider cost saving, greater satisfaction with the telemedicine, and a positive user experience.

The project is registered with the Australian and New Zealand Clinical Trial Registry [ACTRN12614000934640], and ethics approval was granted by Northern Health Human Research Ethics Committee (HREC P/11/14) and Bendigo Health Human Research Ethics Committee (HREC/15/BHCG/44).

## Methods

### Study Design

The TeleGDM trial is a mixed-methods study comprising an exploratory RCT and a qualitative evaluation using semistructured interviews (Figure 1). RCTs are the gold standard for providing evidence for practice [23,24] but have a major limitation of “. . . not tell(ing) the whole story . . . ” [25]. Qualitative methods such as interviews can provide more in-depth information about participant experiences [26] than would otherwise be captured by quantitative methods alone.

**Figure 1 figure1:**
[figure not shown]
Study design flowchart.

### Population, Setting, and Inclusion Criteria

The first group of participants comprises pregnant women diagnosed with GDM who have commenced insulin therapy to control hyperglycemia. These women attended outpatient GDM clinics at two tertiary hospitals between August 30, 2014, and October 30, 2016, inclusive of follow-up. One hospital is in an outer metropolitan region with a catchment population of significant cultural and linguistic diversity. The other is regionally located and serves a population with a rural background. Combined, the two hospitals have approximately 5000 live singleton births annually, and approximately 800 of the pregnancies are affected by GDM.

Women with GDM (patient participant group) are eligible for inclusion if they have a clinical diagnosis of GDM based on the IADPSG criteria following an oral glucose tolerance test [1]. Other eligibility criteria include gestation up to 35 weeks and access to the Internet via a personal computer, smartphone, or tablet. Prepregnancy glucose intolerance, twin pregnancies, GDM not treated with insulin, and other types of diabetes are exclusion factors.

The second group of participants are Credentialed Diabetes Educator Registered Nurses (CDE-RNs) who provide GDM care at the two centers. The CDE-RNs are directly involved in the RCT component of the study and provide care to women with GDM in the course of their usual practice. The number of these clinicians across the two sites is 8; all are requested to complete the clinician assessments for the study.

### Recruitment and Randomization

The women with GDM regularly attend outpatient GDM clinics at the hospitals. It is at these weekly clinics that prospective participants are recruited face-to-face. Clinicians identify potentially eligible patients, give them a study brochure and/or seek permission for referral to the lead researcher or study research assistants. Following referral, participants are approached for face-to-face screening, detailed briefing, consent, randomization, and completion of baseline questionnaires. A 1:1 randomization schedule was generated in STATA 11.0 (StataCorp LP) by an independent statistician. The lead researcher and RAs have no involvement in routine care of the patients.

Some ethnic groups (Indian, Asian, Arabic/Middle Eastern, Pacific Islander, Aboriginal, and African) are considered high risk for GDM [27]. Previous GDM and use of insulin in past pregnancies are also considered high risk factors for GDM. Therefore randomization was stratified according the level of risk (high or low). Stratification avoids group allocation imbalances on factors that have significant influence on prognosis, avoids type 1 error, and improves study power for small trials [28]. Group assignments are concealed in two sets of opaque envelopes; the first set is the randomization schedule for the low risk subgroup and the second for the high risk GDM subgroup. Following consent, the envelopes are consecutively opened for assignment by the recruiter. Clinicians are not blinded to group allocations because they need data from the intervention for clinical care.

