### Telemedicine (Intervention)

The intervention is telemedicine as an adjunct to usual care. The main distinction to usual care is GDM self-monitoring data is shared via a telemedicine system in lieu of paper diaries. The intervention uses a Web-based portal, Online Health Portfolio (OHP) [31], for data sharing and communication between patients and clinicians and is premised upon (1) women with GDM undertaking regular GDM self-monitoring and entering data; (2) timely availability of data to clinicians via the Web-based OHP, hence timely response to the women’s GDM care needs informed by the available data; and (3) upon carrying out advice and feedback the women will better manage GDM and require less frequent appointments. Currently there is no empirical evidence for OHP, and it was chosen for this study on pragmatic reasons and anecdotal accounts of independent endocrinologists who used it in their practice.

Online Health Portfolio is a secure Web-based patient-controlled personal health record that is accessed securely through an Internet browser on a personal computer, smartphone or tablet. It is a proprietary system developed and owned by a vendor who is independent of the study. It uses 256-bit data encryption and 5-minutes inactivity time logout. Besides data entry and preview, the users can have graphical visualization of summary data and trends filtered by pre- or postprandial meal type or time, set up automatic reminders on the internal calendar, and set trigger levels for BGL alerts. Reminders may be forwarded to the patient’s smartphone as a short message service (SMS) text. There is an internal messaging feature within OHP to enable 2-way messaging of free text between clinicians and patients. Clinicians also have the option to send an SMS text to the patient’s smartphone from OHP. Participating patients use their own Internet-connected devices while clinicians use their usual hospital-provided Internet-connected computers. Username and password access to OHP is independent of all other hospital applications and systems. While patients are at liberty to access OHP at any time, clinicians interact with OHP during the course of normal work hours (8:00 AM to 4:30 PM), Monday through Friday. Multimedia Appendix 1 and Multimedia Appendix 2 show of some screenshots of the OHP.

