### Data and Outcomes

Data for research is collected by the lead researcher. This includes weekly extraction of data from OHP for those in the intervention arm in addition to questionnaire outlined below. For controls, photocopies of patients’ paper diaries are obtained when these patients attend their clinic appointments. In addition to these photocopies, where possible, BGL data are directly extracted from the BGL meter via USB cable connection. Finally, once patients have reached the study end point, they also asked to send outstanding self-monitoring data copies of their diaries via email or as photos via smartphone-based multimedia messaging service.

Demographic data together with diabetes self-efficacy and client satisfaction are collected at baseline with follow-up at least 6 weeks after enrollment in the trial. Self-efficacy and satisfaction are measured using the Diabetes Empowerment Scale–Short Form (DES-SF) [33] (Multimedia Appendix 3) and Client Satisfaction Questionnaire–8 Item (CSQ-8) [34,35] (Multimedia Appendix 4). The DES-SF is a shorter version of the original 28-item questionnaire for measuring self-efficacy in people with insulin- or noninsulin-treated diabetes [36]. The original questionnaire has three subscales: managing the psychosocial aspects of diabetes, assessing dissatisfaction and readiness to change, and setting and achieving goals. The longer version has high construct validity and good reliability [18,36]. The shorter version has 8 items, has high reliability (alpha of 0.85), and the scores were found to change positively with improvement in HbA_1c_ [33]. To minimize the burden on participating women we selected the DES-SF to assess diabetes self-efficacy. The CSQ-8 has been used in diabetes research [37] and was assessed for reliability and validity in a childbirth service evaluation [38]. It is reported to have strong reliability, excellent face validity [34,35], good psychometric properties, high client and staff acceptability, and sensitivity to programs of varying quality [37]. The CSQ-8 is available under paid license while the DES-SF is free with appropriate attribution. Both the DES-SF and SCQ-8 questionnaires are self-completed face-to-face or administered over the phone at baseline and at least six weeks from enrollment. Further information on outcomes and data collection time points is provided in Table 1.

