### Data Preparation and Analysis

Quantitative data analysis will be performed using Stata/IC 13.1 (StataCorp LP) with an intention to treat analysis. Missing data for the primary outcome is expected to be minimal as all patient appointments and outcomes are recorded. For the DES and CSQ-8 losses to follow-up will employ last observation carried forward for missing values. Since case BGL data is serial and expected to be nonlinear, case mean of nearby data points imputation will be used for missing data.

Summary univariate statistics will be used to describe the study populations and compare study groups at baseline. Categorical variables will be summarized as raw numbers and percentages and between groups comparisons will utilize chi-square statistics. Multivariate statistical analysis will be performed to compare the groups on primary and secondary outcomes. In addition, survival analysis will be performed to explore time to reach glycemic stability. Statistics will be reported with standard deviations or 95% confidence intervals as appropriate. Statistical significance will be indicated by *P*<.05.

Patient and clinician interviews will undergo thematic analysis supported by NVivo 11 (QSR International). The interview transcripts will be analyzed separately for each participant group using an inductive approach to identify and/or infer themes and codes from the transcripts. Further themes will be classified according to the dimensions of telehealth evaluation framework [41].

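### As the enrolment steps are listed, the baseline DES-SF and CSQ-8 come after randomization, so women can complete these self-reported scores knowing their arm

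*Protocol article*

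**What the plan says.** Recruitment and Randomization gives the enrolment steps as a list: "participants are approached for face-to-face screening, detailed briefing, consent, randomization, and completion of baseline questionnaires". The same section adds: "Following consent, the envelopes are consecutively opened for assignment by the recruiter". It also says: "Clinicians are not blinded to group allocations because they need data from the intervention for clinical care". No blinding of the women is described. Under Telemedicine (Intervention), the contrast between the arms is one a woman cannot miss: "The main distinction to usual care is GDM self-monitoring data is shared via a telemedicine system in lieu of paper diaries".

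Data and Outcomes fixes the two measurement times: "Demographic data together with diabetes self-efficacy and client satisfaction are collected at baseline with follow-up at least 6 weeks after enrollment in the trial". On mode, it says that the DES-SF and CSQ-8 "questionnaires are self-completed face-to-face or administered over the phone at baseline and at least six weeks from enrollment". Table 1 lists both self-efficacy and satisfaction as secondary outcomes, at baseline and at 6 weeks or later.

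Data Preparation and Analysis states the missing-data rule: "For the DES and CSQ-8 losses to follow-up will employ last observation carried forward for missing values". It plans a multivariate comparison of the arms on primary and secondary outcomes, without naming a model for these two scores.

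**The concern.** A baseline score is useful because allocation cannot have influenced it. If the form is filled in after the envelope is opened, that protection is lost. Both instruments are self-reports, of confidence in managing diabetes and of satisfaction with care. Being pleased or disappointed with the assigned arm could move either score, or affect whether the form is completed at all.

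Three uses of the score would then be exposed. It would be an unsafe reference for change or covariate. It would be a less reliable check that the arms were alike at entry. And with only one baseline and one follow-up, LOCF makes it the outcome value for every woman without a follow-up form. Greater satisfaction with telemedicine is part of the stated hypothesis, so the direction of a modest bias would matter to the reader.

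**Working it through.** No figure in the protocol depends on the order of steps, so there is nothing to reproduce. The check has two parts.

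**Order of steps**

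- The listed sequence is screening, briefing, consent, randomization, questionnaires. The first four items are in time order, which makes it natural to read the fifth that way too.
- The separate sentence on envelopes ties opening to consent. It mentions no form in between.
- Data and Outcomes says only that the scores are taken at baseline. It does not place them before assignment.
- No visible text gives a different order.

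**Size, as an illustration only**

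The documents give neither a shift nor a correlation, so these inputs are assumptions:

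- *b*: the amount by which knowing the arm raises the baseline score in the telemedicine arm relative to control, 0.1 to 0.3 SD. If the shift runs the other way, every sign below reverses.
- *rho*: the within-arm correlation of baseline with follow-up, 0.3 to 0.7, with equal SDs at both times.
- *m*: the share of women whose follow-up is filled by LOCF, 0.30. The Sample Size section mentions 30% attrition when arguing for the primary outcome; it is borrowed here and is not a forecast for these forms. Loss is taken as equal across arms and unrelated to score.

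Bias means the part of the telemedicine-minus-control contrast that is due to *b* alone. Any dilution of a true effect by LOCF is a separate matter.

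Without LOCF:

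- Change score: bias = -*b*, so -0.1 to -0.3 SD.
- ANCOVA: bias = -*rho* × *b*, from -(0.3 × 0.1) = -0.03 SD to -(0.7 × 0.3) = -0.21 SD.
- Follow-up scores only: 0.

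With LOCF, at *b* = 0.2, *rho* = 0.5, *m* = 0.30:

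- The follow-up contrast receives *m* × *b* = 0.30 × 0.2 = +0.06 SD. This is the whole bias if follow-up scores alone are compared.
- Change score: 0.06 - 0.20 = -0.14 SD. Women filled by LOCF have zero change and so contribute no bias.
- ANCOVA: the pooled slope becomes 0.7 × 0.5 + 0.3 × 1 = 0.65, so the bias is 0.06 - 0.65 × 0.2 = 0.06 - 0.13 = -0.07 SD.

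The LOCF term therefore partly offsets the change-score and ANCOVA biases. If *b* = 0, every entry is zero.

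For scale, 50 women per arm (100 randomized 1:1) can detect about 0.57 SD with 80% power at two-sided 5%. The LOCF results above are 0.06/0.57 = 11%, 0.07/0.57 = 12% and 0.14/0.57 = 25% of that.

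**The case against.** The order is inferred from a list that contains no word such as then. Following consent does not mean immediately after it, so a form could come between consent and the envelope. The Figure 1 flowchart, where one would look for the order, is not visible. This stands as a limit on certainty. It does not remove the point, because the plain reading puts randomization first and no visible text says otherwise.

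The protocol names neither a change score nor ANCOVA for these outcomes. This also stands: those biases apply only if such a model is used. If follow-up scores are compared directly, only the LOCF route remains.

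The reach is narrow. Two secondary scores in an exploratory trial are involved. At enrolment both arms have received only usual care, so an arm-specific shift in satisfaction is possible but not shown.

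A reader might infer more than the documents support:

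- That the baseline was in fact distorted. The documents show only that it can be.
- That the forms were filled in under the recruiter's eye. Nobody is named as present, and telephone administration is allowed.
- That intervention women answered after their portal induction. Induction takes place upon enrolment, but its order relative to the forms is not stated.
- That the main result is compromised. Service utilization comes from the outpatient activity dataset and medical records and does not use these scores.

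**Conclusion.** The point holds in a limited form. As written, the enrolment sequence lets women complete the baseline DES-SF and CSQ-8 knowing their arm, and the LOCF rule carries those scores into the outcome for women lost to follow-up. Whether a shift occurred, and in which direction, is unknown.

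Under the assumptions shown, the bias is small to moderate, and its sign depends on the analysis. Change-score and ANCOVA results would lean against the arm whose baseline was raised, and a follow-up-only comparison with LOCF would lean towards it. A reader could not tell from the result which applies. The conclusion rests on reading the list in time order and would fall away if Figure 1 or actual practice places the forms before assignment. It is worth correcting because the remedy is simple, not because the trial's main conclusion is at risk.

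**What to change.** For women still to be recruited, have the DES-SF and CSQ-8 completed after consent and before the next envelope is opened, and state that order in Recruitment and Randomization. If this is already the practice, correcting the sentence is enough.

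For women already enrolled, record where it is known whether each baseline form came before or after assignment. Add a sensitivity analysis of observed follow-up scores by arm, with no adjustment for a post-assignment baseline and no LOCF values.

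The change uses the same forms and staff at the same visit, but it is not free. Recruitment was already underway when the article was submitted, so the data would mix pre- and post-assignment baselines. The order may not be recoverable for every woman. The sensitivity analysis gives up some precision by dropping the baseline covariate and the filled-in values. It can still be done if recruitment has closed.
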